### Statistical analysis

Continuous variables will be described using means and standard deviations or median and range in the case of asymmetric data distribution. Categorical variables will be presented as numbers and frequencies, and comparisons will be made using the chi-square test or Fisher’s exact test as appropriate. All time-to-event outcomes will be summarized using Kaplan-Meier survival estimates and compared among treatment groups using log-rank tests. An array of prespecified and exploratory subgroup analyses of the primary and major secondary endpoints will be performed. Statistical significance will be considered at *P* < 0.05. A statistical package (SPSS 16.0) will be used for analysis. The individual will be considered as a unit of analysis.

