## Methods/design

### Study design

This is a prospective, multicenter, randomized clinical trial that should demonstrate the non-inferiority of the BuMA Supreme stent compared with the Xience stent on neointimal healing response evaluated by optical coherence tomography (OCT). In the current trial, the following devices will be used: BuMA Supreme stent – Biodegradable Polymer SES Coated Coronary Stent System manufactured by SINO Medical Sciences Technology Inc. and the Xience V/Prime/Xpedition stent – Durable Polymer everolimus-eluting Stent System manufactured by Abbott Company. A full range of commercially available guiding catheters, balloon catheters, and guidewires will be readily available.

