### Study endpoints and clinical follow-up

The primary endpoint is the stent-strut neointimal coverage rate (%) by OCT assessment at 1 month and 2 months, respectively. Secondary OCT endpoints include neointima hyperplasia area/volume, neointimal hyperplasia thickness and the stent-strut malapposition at 1 or 2 months’ follow-up, respectively. Secondary angiographic endpoints include LLL, restenosis rate of in-stent/in-segment at 1 or 2 months’ follow-up, respectively. Secondary clinical endpoints include device/lesion/clinical success rate, device-oriented composite endpoints and its individual components, other serious adverse (MI, TLR and stent thrombosis) and bleeding events at 1 or 2, 3, 6 months, 1 year and 2 years.

Target lesion failure was defined as the composite of cardiac death, target vessel myocardial infarction (MI), and ischemia-driven TLR. MI was adjudicated according to the third universal definition of MI [10]. Stent thrombosis (definite and probable) was defined according to the Academic Research Consortium (ARC) classification. All clinical events were adjudicated by an independent Clinical Events Committee (CEC). Device success was defined as attainment of < 30% residual stenosis of the target lesion by visual assessment. Lesion success was defined as attainment of < 30% residual stenosis, TIMI 3 flow, and no residual dissection or thrombosis of the target lesion using any percutaneous method. Clinical success was defined as attainment of lesion success of the target lesion and no in-hospital major adverse cardiac event.

Angiography and OCT investigations are conducted at 1 or 2 months post PCI. Clinical follow-up visits or telephone follow-up will be conducted at the first, second, third, sixth month, or 1 to 2 years post PCI.

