### Sample size of clinical trials

The study’s primary endpoint was stent-strut neointimal coverage rate (%) by OCT assessment at the first or second month. Using a two-sided α of 0.05, 20 subjects were enrolled in each group. It was assumed that 1.5 stents would be implanted in each patient with 200 stent struts (20 mm length) for each stent. Regarding a 20% drop-out rate, 4800 stent struts were estimated to be tested. Assuming a neointimal coverage rate for both the BuMA and Xience stents of 70%, and a non-inferior margin of 3.6% at the first month, stent struts would have at least 97% power to detect that the Supreme group show non-inferiority to that of the Xience group. Assuming a neointimal coverage rate for both BuMA and Xience stents of 85%, and a non-inferior margin of 2.4% at the second month, stent struts would have at least 91% power to detect that the Supreme group shows non-inferiority to that of the Xience group. Since a competition mechanism is introduced into this multicenter study, no single center will enroll more than 40% of the patients.

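### The stated analysis consists of difference tests at P < 0.05 and does not use the 3.6- and 2.4-point margins, so it does not test the non-inferiority objective on which the trial is sized

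*Protocol article*

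**What the plan says.** All references are to the protocol article.

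- **Objective** (Study design; the Abstract agrees): the trial "should demonstrate the non-inferiority of the BuMA Supreme stent compared with the Xience stent on neointimal healing response".
- **Primary endpoint** (Study endpoints and clinical follow-up): "The primary endpoint is the stent-strut neointimal coverage rate (%) by OCT assessment at 1 month and 2 months, respectively".
- **Sizing** (Sample size of clinical trials): "Using a two-sided α of 0.05, 20 subjects were enrolled in each group". Each patient is expected to contribute struts on the basis that "1.5 stents would be implanted in each patient with 200 stent struts (20 mm length) for each stent". Then: "Regarding a 20% drop-out rate, 4800 stent struts were estimated to be tested". With 70% coverage in both arms and "a non-inferior margin of 3.6% at the first month", power is given as at least 97%. With 85% in both arms and a margin of 2.4% at month 2, it is given as at least 91%.
- **Analysis** (Statistical analysis): continuous variables are summarised. For categorical variables "comparisons will be made using the chi-square test" or Fisher's exact test. Time-to-event outcomes are compared by log-rank test. Significance is set at P < 0.05, and the individual is the unit of analysis. The section contains no margin, confidence limit or non-inferiority hypothesis.

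**The concern.** The objective and the sample size describe one test, and the analysis section describes others. Chi-square, Fisher and log-rank tests address the null hypothesis of no difference. Non-inferiority needs the null hypothesis of a deficit at least as large as the margin to be rejected, and no rule for that is given.

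The unit of analysis adds a second gap. With the individual as unit, the primary endpoint is a percentage per patient, which is a continuous variable, and no between-group comparison is named for continuous variables. The only named test that could be applied to coverage is a chi-square on covered and uncovered struts, which would contradict the stated unit.

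At stake is the trial's main conclusion. If the rule is not fixed in advance, the unit, the interval and the criterion can be chosen once the data are known. The authors also intend the results to inform later work on antiplatelet duration.

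**Working it through.** **1. Reproduce the stated power.** Inputs from the sample size section: 20 patients per arm, 1.5 stents per patient, 200 struts per stent, 20% drop-out.

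Struts per arm: 20 × 1.5 × 200 × 0.8 = 4800.

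Power = Φ(margin/SE − z), with SE = √(2p(1−p)/n) and z = 1.96 (two-sided 0.05, that is one-sided 0.025).

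- Month 1: SE = √(2 × 0.70 × 0.30/4800) = 0.00935; 0.036/0.00935 = 3.85; Φ(3.85 − 1.96) = 97.05%. Stated: 97%.
- Month 2: SE = √(2 × 0.85 × 0.15/4800) = 0.00729; 0.024/0.00729 = 3.29; Φ(3.29 − 1.96) = 90.9%. Stated: 91%.

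With 2400 struts per arm the results are 77.7% and 64.4%; with 6000 they are 99.0% and 95.7%. With 4800 per arm but one-sided 0.05 they are 98.6% and 95.0%. The powered test is therefore identifiable: margins in absolute points, read against a 95% interval, with 4800 independent struts per arm.

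**2. Compare with the stated analysis.** That test does not appear in the Statistical analysis section. If the true rates are equal, as planned, a two-sided 5% difference test is significant in favour of BuMA 2.5% of the time. Only that outcome would imply non-inferiority.

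**3. Where the two tests disagree, on the plan's own strut inputs.** The difference test is significant beyond 1.96 × SE. Non-inferiority is met for an observed deficit up to margin − 1.96 × SE.

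- Month 1: significant beyond 1.83 points; non-inferior up to 3.60 − 1.83 = 1.77 points.
- Month 2: significant beyond 1.43 points; non-inferior up to 2.40 − 1.43 = 0.97 points.

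An observed deficit of 1.77 to 1.83 points (month 1) or 0.97 to 1.43 points (month 2) is thus non-significant yet fails non-inferiority.

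**4. Effect of the unit of analysis.** The article gives neither an intraclass correlation (ICC) nor a patient SD, so both are assumptions here. For clustering, 300 struts per patient (1.5 × 200) give a design effect of 1 + 299 × ICC, and SE is multiplied by its square root. At ICC 0.01 the design effect is 3.99 and 4800 struts are worth 4800/3.99 ≈ 1203. For a per-patient mean with 16 per arm (20 × 0.8), SE = SD × √(2/16), with 30 degrees of freedom and the noncentral t distribution. At SD 10, SE = 3.54 points.

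In the table, NI power assumes equal true coverage. The last two columns give the chance that a difference test has P > 0.05 when the true deficit equals the margin.

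| Assumption | NI power, month 1 | NI power, month 2 | P > 0.05 at margin, month 1 | P > 0.05 at margin, month 2 |
|---|---|---|---|---|
| Independent struts (plan) | 97% | 91% | 3% | 9% |
| ICC 0.01 | 49% | 38% | 51% | 62% |
| ICC 0.05 | 16% | 13% | 84% | 87% |
| ICC 0.20 | 7% | 6% | 92% | 93% |
| Patient SD 5 | 50% | 26% | 50% | 74% |
| Patient SD 10 | 17% | 10% | 83% | 90% |
| Patient SD 15 | 10% | 6% | 90% | 93% |

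A correct non-inferiority test would pass about 2.5% of the time when the true deficit equals the margin.

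**The case against.** The analysis section is a generic paragraph in a condensed article. The chi-square wording applies to categorical variables, and the section mentions the primary endpoint only in connection with subgroup analyses. The sample size section gives the endpoint, alpha and both margins, from which a reader can infer a 95% interval read against the margin. The full protocol or an analysis plan may state that rule. This stands as a limit: the defect is in the section as written, and the right rule may exist elsewhere. It does not remove the point, because the section is not silent. It sets out tests and a criterion, and these do not match the test that was powered. The inference from the sample size section also leaves the unit unsettled, since that section counts struts and the analysis section counts individuals.

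Four stronger readings are tempting, and the article does not support them.

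- *That the analysis cannot establish non-inferiority.* A significant result favouring BuMA would imply it, though that is unlikely under equal rates.
- *That a non-significant P will be taken as non-inferiority.* The article does not say so.
- *That such a misreading would err 83% to 90% of the time.* Those figures need a patient SD of 10 or 15 points, which the article does not give. On its own independent-strut inputs the rates are 3% and 9%.
- *That a one-sided P would be judged at 0.05, doubling the planned error.* The sample size section specifies a two-sided alpha of 0.05, and no one-sided P is mentioned.

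**Conclusion.** The point holds as a mismatch between the stated analysis and the powered hypothesis. The objective and sample size call for a margin-based test, which the stated power figures confirm by reproducing at 97.05% and 90.9%. The analysis section offers only difference tests at P < 0.05, and it names no comparison for the endpoint at the unit it specifies.

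The 2.5% chance that a difference test would itself imply non-inferiority needs only the plan's assumption of equal rates and a valid 5% test. The chance that a deficit equal to the margin goes undetected by a difference test can be given only as a range: from 3% (month 1) and 9% (month 2) with independent struts, through 51% and 62% at ICC 0.01, to above 90% at the highest ICC and SD tried. It matters only if non-significance is misread, which the article does not propose.

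**What to change.** In the Statistical analysis section, state:

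- in each cohort, non-inferiority is concluded if the lower limit of the two-sided 95% confidence interval for coverage, BuMA Supreme minus Xience, lies above -3.6 points (month 1) or -2.4 points (month 2);
- the interval is computed from per-patient coverage rates, or by a method that allows for clustering of struts within patients;
- difference tests at P < 0.05 apply to the secondary comparisons.

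The text change is one paragraph and needs no new data. It does have a consequence that should be stated openly: with the patient as unit, or with clustered error, the claims of 97% and 91% power no longer stand. Examples are about 49% and 38% at ICC 0.01, or about 17% and 10% at a patient SD of 10 points with 16 per arm. The power statement must be restated with an ICC or patient SD that the sponsor can justify, and the trial may prove too small for these margins.

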## Discussion

PCI is widely used for patients with CAD all over the world. Compared with BMS, DES reduce the rate of restenosis from 20–35% to 10% and reduce the consequent need for TLR. However, DES increases the risk of late stent thrombosis, death and MI [11–13]. A previous study [12] reported that the incidence of definite stent thrombosis was increased by 0.53% (CI 0.44–0.64) per year, and the cumulative rate of definite stent thrombosis was 3.3%, combined incidence of definite stent thrombosis and the probable stent thrombosis was 5.7% in 4 years. At present, some studies have regarded endothelialization as one of the important factors that may reduce late thrombosis and then reduce cardiovascular events; therefore, research on DES has focused on how to promote the endothelialization. The ideal DES is to maximize the inhibition of smooth-muscle-cell proliferation and migration, minimize changes of structure and functional recovery of endothelial cell, and promote faster healing of endothelium [14, 15]. The second generation of drug-eluting stents (DES) has emerged with more biocompatible durable polymer coatings on thin-strut stents that have shown better safety than first-generation DES [16, 17]. The Biodegradable Polymer (BP)-DES, BuMA Supreme stent, was developed to prevent polymer-related adverse effects [18].

DAPT treatment increases from 1 month of the BMS to 6–12 months of DES post procedure, or even longer, which increases the risk of bleeding. Research on how to shorten the DAPT period after the new DES implantation will benefit relatively high-bleeding-risk patients. Studies showed that one out of seven to eight CAD PCI patients has a relatively high risk of bleeding, so clinicians need to evaluate bleeding and ischemic risk after DES, and adjust their DAPT treatment to obtain better clinical results [2].

In the recent 10 years, OCT has been widely used as an intravascular imaging technology to determine the morphology of the implanted stents, whereby high-resolution intravascular images can be obtained quickly – especially accurate results of stent-strut coverage in the vessel [19, 20]. For example, Ishigami K et al. observed stent-strut coverage of the first-generation sirolimus eluting stent (SES) at 9 months, 9–24 months and 25 months, respectively, and they found that only 17.6% of the SES was completely covered at 25 months. Delayed neointimal coverage was observed in patients with small blood vessels, complex lesions, high-lipid and high-calcium lesion or diabetics [21]. OCT was a reliable method for assessing the neointimal formation of stent strut post PCI, and it provided a good match to the resemblance of “optical biopsy.”

The research and development of stents is focused on the materials and coating composition of stents in China [22]. OCT is rarely used to evaluate vessel healing after new stent implantation. We have evaluated new BuMA DES strut coverage at 9 months by OCT in 2010, which showed that stent-strut coverage rate in BuMA stent was 94.3%, which was superior to that of the Endeavor stent [23]. The PANDA-III study with 2348 samples showed a statistically significant difference in the incidence of definite and probable stent thrombosis (0.7% vs. 1.4%) at 1 year, that is less stent thrombosis than occurred in the BuMA stent [24]. Moreover, in OCT follow-up at 3 months, the percentage of stent-strut coverage was significantly higher in the BuMA vs. the EXCEL group (strut level: 94.2% vs. 90.0%, *P* < 0.01) [5]. It showed that the design concept and technology of BuMA stent is good to promote early and complete healing of the neointima at a corresponding time after PCI at 3 months. The LEADERS FREE study also used large samples to compare the efficacy and safety of implantation of BMS and new DES in patients with CAD; 1-year follow-up showed that the efficacy and safety of the new DES group was superior to that of the BMS group [6, 25]. The OCT study of neointimal coverage has been reduced from 9 months to 3 months at present [5]; one purpose of this study is whether we could learn more about stent-strut coverage rate at 2 months and 1 month, which will help to conduct further study of an adjusted postoperative DAPT regimen. The evidence may provide clinicians and patients with more precise imaging evidence in DAPT regimens, especially more benefit for patients with a relatively high bleeding risk.

For BuMA stents that used international-patent, electronic-grafted (eG) technology, common problems, such as stent surface cracking and residue after drug release, are solved successfully, leading to rapid and complete endometrial healing and inhibition of late stent thrombosis. This feature is more conducive to helping patients with a relatively high risk of bleeding to adjust their DAPT treatment regimen. Based on the design of the previous generation of BuMA stents, the stent metal platform of the BuMA Supreme changed from 316 L stainless steel to L605 cobalt chromium – with thinner stent strut and better stent effects in contrast imaging and flexibility. Meanwhile, the thinner stent strut may further benefit the endothelium healing, which will bring the patients more safety benefits.

In conclusion, this is the first study to compare the strut coverage of the XIENCE stent with that of the BuMA Supreme sirolimus-eluting cobalt-chromium stent, which has a shorter drug elution on optical coherence tomography (OCT) 1 or 2 months after implantation; and it will give us accurate imaging evidence on neointimal formation of the BuMA Supreme stent and the Xience stent at 1–2 months post PCI. The result should inspire further exploration and adjustment of DAPT treatments Additional file 1.

## Abbreviations

ARC: Academic Research Consortium
BMS: Bare metal stent
CAD: Coronary artery disease
DAPT: Dual anti-platelet therapy
DES: Drug-eluting stents
LLL: Late lumen loss
LVEF: Left ventricular ejection fraction
MLD: Minimal lumen diameter
OCT: Optical coherence tomography
PCI: Percutaneous coronary intervention
PLGA: Poly-lactic-co-glycolic acid
PTCA: Percutaneous transluminal coronary angioplasty
QCA: Quantitative coronary angiography
RVD: Reference vessel diameter
SES: Sirolimus-eluting stent
TLF: Target-lesion failure
TLR: Target-lesion revascularization
ZES: Zotarolimus-eluting stents
